#### Effect evaluation primary outcome parameter

To evaluate the difference in clinical effectiveness of both follow-up protocols, the number of radiographs with treatment consequences will be divided by the total number of radiographs in each subgroup (pre-treatment, post-brace, post-surgery). To compare the primary outcome between the PE-FU group and the S-FU group, Pearson’s chi-square test is used. To evaluate the effect according to subgroups, linear mixed-effects models that account for repeated measurements will be performed, adjusted for scoliosis center and relevant baseline covariates. Assumptions of linear mixed modelling will be assessed and if needed variable transformations will be performed. Furthermore, for each subgroup the results of the RCT follow-up protocols will be compared with the similar preference cohort to indicate generalizability of study results.

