### Explanation of the sample size calculation per subgroup

#### Pre-treatment group

In the literature, a 23% risk of curve progression was described [25] (i.e., comparator; usual/S-FU care). In the pre-treatment group, routine follow-up takes place every 6 months for a duration of 24 months (i.e., 4 follow-up assessments). Consequently, the incidence of progression per radiograph is 5.75% (i.e., 23%/4) for the control group/S-FU group. Based on the literature and expert opinion, a 5% margin is allowed for the PE-FU and 20% extra radiographs are expected for this group. The margin of 5% results in 28% risk of curve progression for the investigational group/PE-FU group (23% + 5% = 28%). Therefore, the incidence of progression per radiograph is expected to be 23.3% (i.e., 28%/1.20) for the PE-FU group (intervention/investigational group). For the increase in incidence/radiograph from 5.75% to 23.3%, the calculated sample size is 60 patients per arm (given a 95% CI and 80% power). Taking into account the expected loss to follow-up/dropout (10%), the final sample size is 66 patients for each treatment arm in the pre-treatment group.

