#### Post-brace group

In this group also, 23% of the patients have a risk of curve progression [14] (i.e., comparator; usual/S-FU care). The routine follow-up takes place every 6 months for a duration of 24 months (i.e., 4 follow-up assessments). Therefore, the incidence of progression per radiograph is 5.75% (i.e., 23%/4) for the control group/S-FU group. With a 5% margin for the PE-FU group, the risk of curve progression for the investigational group/PE-FU group will be 28%. We expected an increase of 15% based on expert opinion in the number of radiographs in the PE-FU post-brace group. Consequently, the expected incidence of progression per radiograph is 24.3% (i.e., 28%/1.15) in the PE-FU group. Based on the increase in incidence per radiograph from 5.75% to 24.3%, each arm of the post-brace group was calculated to consist of 55 patients (given a 95% CI and 80% power). With an expected loss to follow-up/dropout of 10%, each treatment arm of the post-brace group includes 61 patients.

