#### Post-surgery group

Based on a recent study among patients with AIS, no progression in the surgical area is expected [31]. Adding-on is a radiological complication that indicates progression of the curve under or above the instrumented curve. The expert opinion for clinically relevant prevalence of adding-on is 10% (i.e., comparator; usual care), with a 5% margin for PE-FU (i.e., 15%). The routine follow-up takes place at 3, 12, and 24 months after surgery (i.e., 3 follow-up assessments with biplanar full spine radiographs = 6 radiographs). The incidence of adding-on per radiograph is 1.7% (i.e., 10%/6) for the control group/S-FU group. The risk of adding-on for the investigational group/PE-FU group will be 15% (prevalence of 10% with a 5% margin for PE-FU). The expected extra number of radiographs in the post-surgery group is 5% (expert opinion). Therefore, the incidence of adding on per radiograph is expected to be 14.3% (i.e., 15%/1.05). For the increase in incidence/radiograph from 1.7% to 14.3%, the calculated sample size is 69 patients per arm (given a 95% CI and 80% power). Considering a 10% dropout and/or loss to follow-up, the final sample size is 76 patients per treatment arm for the post-surgery group.

Based on the above (literature and expert opinion), for this study a total of 812 patients is required (alpha 0.05; power 0.80). This means 66 per arm for the RCT pre-treatment, 61 per arm for the RCT post-brace, and for the RCT post-surgery 76 per arm (subtotal of patients in the RCTs is 406). The preference cohorts consist of the same arms as the three RCTs. For each arm (preference cohort) a similar number of patients is required (subtotal of patients in the preference cohorts is 406 patients).

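### The 60, 55 and 69 reported as patients per arm for 80% power are numbers of radiographs; on the plan's own inputs the planned test has about 97% power

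*Protocol article*

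**What the plan says.** The protocol article makes the radiograph the unit of the primary outcome. Under the data analysis heading on the primary outcome, "the number of radiographs with treatment consequences will be divided by the total number of radiographs in each subgroup", and the arms are compared by Pearson's chi-square test.

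The appendix derives the sample size from rates on that scale. For S-FU in the pre-treatment group: "Consequently, the incidence of progression per radiograph is 5.75% (i.e., 23%/4) for the control group/S-FU group". For PE-FU: "the incidence of progression per radiograph is expected to be 23.3% (i.e., 28%/1.20) for the PE-FU group". The 28% is the 23% patient risk plus a 5-point margin. The result is then given in patients: "For the increase in incidence/radiograph from 5.75% to 23.3%, the calculated sample size is 60 patients per arm".

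The post-brace section does the same: "Based on the increase in incidence per radiograph from 5.75% to 24.3%, each arm of the post-brace group was calculated to consist of 55 patients". The post-surgery section divides 10% by 6 films for S-FU and 15% by 1.05 for PE-FU, and reports 69 patients per arm for 1.7% vs 14.3%. With 10% added for dropout, the three figures become 66, 61 and 76. These make up the RCT subtotal of 406, which is doubled: "for this study a total of 812 patients is required (alpha 0.05; power 0.80").

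**The concern.** A two-proportion formula returns the number of independent observations per arm in the unit of the proportions it is given. With per-radiograph proportions, the answer is radiographs. The appendix calls it patients, although its own divisors say that an S-FU patient contributes 4 radiographs (6 post-surgery) and a PE-FU patient 1.05 to 1.20. No step converts one unit to the other.

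Two features of the planned comparison are therefore missing from the calculation: the arms differ more than threefold in numbers of radiographs, and radiographs from one patient are not independent. The 80% power attached to all three RCTs, and to the total of 812, is then not the power of the test that will be run.

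**Working it through.** **Inputs, all from the appendix.** Pre-treatment: 23%/4 = 5.75% vs 28%/1.20 = 23.3%. Post-brace: 23%/4 = 5.75% vs 28%/1.15 = 24.3%. Post-surgery: 10%/6 = 1.7% vs 15%/1.05 = 14.3%. Alpha is 0.05 and power 0.80. Two-sided testing is inferred from the 95% CI. The extra radiographs are read as 1.20, 1.15 and 1.05 per PE-FU patient because the appendix divides by those numbers.

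**Step 1: reproduce the stated figures.** Equal arms, unpooled variance:

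n = (1.960 + 0.8416)² × [p1(1−p1) + p2(1−p2)] / (p2−p1)², with (1.960 + 0.8416)² = 7.849.

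- Pre-treatment: 7.849 × (0.0542 + 0.1787) / 0.1755² = 59.4, rounded up to 60.
- Post-brace: 7.849 × (0.0542 + 0.1840) / 0.1855² = 54.3, rounded up to 55.
- Post-surgery: 7.849 × (0.0167 + 0.1226) / 0.126² = 68.8, rounded up to 69.

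All three match. Multiplying by 1.10 gives 66, 60.5 (61) and 75.9 (76). So 60, 55 and 69 are independent radiographs per arm.

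**Step 2: convert patients to radiographs.**

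- Pre-treatment, 60 patients: 60 × 4 = 240 vs 60 × 1.20 = 72.
- Post-brace, 55 patients: 55 × 4 = 220 vs 55 × 1.15 = 63.
- Post-surgery, 69 patients: 69 × 6 = 414 vs 69 × 1.05 = 72.

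**Step 3: power of the chi-square test on those totals** (normal approximation, independent radiographs, unrounded rates):

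power = Φ[(p2 − p1 − 1.96·s0) / s1], where s0 = √{p̄(1−p̄)(1/n1 + 1/n2)}, p̄ is the pooled proportion, and s1 = √{p1(1−p1)/n1 + p2(1−p2)/n2}.

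| Subgroup | p2 − p1 | s0 | s1 | z | Power |
|---|---|---|---|---|---|
| Pre-treatment | 0.1758 | 0.0400 | 0.0521 | 1.87 | 96.9% |
| Post-brace | 0.1860 | 0.0426 | 0.0562 | 1.82 | 96.6% |
| Post-surgery | 0.1262 | 0.0236 | 0.0416 | 1.92 | 97.3% |

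**Step 4: several radiographs per patient.** Simulating the chi-square test with at most one treatment consequence per patient gives 98.3%, 97.8% and 98.9%. With an assumed within-patient correlation of 0.1, 0.3 or 0.5 (not in the documents), pre-treatment power is 95.7%, 92.7% or 89.1%.

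**Step 5: sensitivity to the counting rule.** These counts depart from the appendix's calculation and are assumptions.

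- Post-surgery by examination in both arms (3 vs 1.05 per patient; 3.3% vs 14.3%; 207 vs 72): about 85%.
- Pre-treatment with the baseline assessment counted (5 vs 2.2; 4.6% vs 12.7%; 300 vs 132): about 82%.
- Pre-treatment with every film counted, baseline included (7 vs an assumed 4.2; 3.3% vs 6.7%; 420 vs 252): about 53%.

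**Step 6: could the figures be patient-level after all?** For 23% vs 28% with 60 patients per arm, power is about 9%; for 10% vs 15% with 69 per arm, about 14%. The stated 80% does not belong to a patient-level test either.

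**The case against.** The strongest reply is that the mistake does no harm. Sixty radiographs need only 60/4 = 15 S-FU patients or 60/1.20 = 50 PE-FU patients, so 60 patients per arm are enough on both sides and power exceeds what was promised. That stands, and it is why the numbers to be recruited need not change.

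It is also fair to say that the plan does not ignore repeated radiographs. The section on the primary outcome also plans mixed-effects models that account for repeated measurements, so the omission concerns the sample size calculation only. With at most one consequence per patient, the simulation shows no loss of power from repetition.

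Neither reply makes 60, 55 and 69 numbers of patients or makes 80% the power of the chi-square test. Nor is this a detail left to another document, because the calculation is written out in full in the appendix.

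A reader might go further and infer that the trial, or the post-surgery RCT in particular, is underpowered. The documents do not support that. The post-surgery section divides by 6 films, and at that rate power is about 97%. Even the examination count, which that section does not use, leaves about 85% for the planned test. Going lower post-surgery takes a further change, such as a different test, strong assumed correlation or removal of the 5-point margin, which is a separate matter.

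**Conclusion.** The unit error is real and affects all three RCTs. The stated figures are reproduced exactly only by treating each patient as one radiograph. On the document's own rates and radiographs per patient, the planned test has about 97% power in each subgroup rather than 80%, so the error is conservative.

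This rests on the appendix's event rates, on 4 (or 6) vs 1.05 to 1.20 radiographs per patient, and on 10% dropout leaving about 60, 55 and 69 evaluable patients per arm. It is not a fixed property of the trial. The article does not say whether baseline radiographs enter the denominator, or whether a biplanar examination counts as one or two. Under the other counts tried, power is about 85% (post-surgery) or 82% (pre-treatment), and about 53% (pre-treatment) only if every film including baseline is counted.

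For the same reason a reader should not infer that recruitment could be cut. About 29, 28 and 29 patients per arm would give 80% on the appendix's counts, but that margin shrinks or disappears under another counting rule.

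**What to change.** Keep 66, 61 and 76 patients per arm. In the appendix and the analysis plan:

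1. State which radiographs enter the primary denominator (baseline or not, the 24-month radiograph or not), and use one unit, film or examination, in both arms.
2. Restate power for each subgroup from the expected radiographs per patient and arm in that unit, with unequal totals and a variance that allows for several radiographs per patient. Show a range for any assumed within-patient correlation.
3. Stop describing 60, 55 and 69 as the numbers of patients needed for 80% power.

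The cost is a revised paragraph per subgroup and a short recalculation. Recruitment, randomization and data collection are unaffected.

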#### Post-brace group

In this group also, 23% of the patients have a risk of curve progression [14] (i.e., comparator; usual/S-FU care). The routine follow-up takes place every 6 months for a duration of 24 months (i.e., 4 follow-up assessments). Therefore, the incidence of progression per radiograph is 5.75% (i.e., 23%/4) for the control group/S-FU group. With a 5% margin for the PE-FU group, the risk of curve progression for the investigational group/PE-FU group will be 28%. We expected an increase of 15% based on expert opinion in the number of radiographs in the PE-FU post-brace group. Consequently, the expected incidence of progression per radiograph is 24.3% (i.e., 28%/1.15) in the PE-FU group. Based on the increase in incidence per radiograph from 5.75% to 24.3%, each arm of the post-brace group was calculated to consist of 55 patients (given a 95% CI and 80% power). With an expected loss to follow-up/dropout of 10%, each treatment arm of the post-brace group includes 61 patients.

#### Post-surgery group

Based on a recent study among patients with AIS, no progression in the surgical area is expected [31]. Adding-on is a radiological complication that indicates progression of the curve under or above the instrumented curve. The expert opinion for clinically relevant prevalence of adding-on is 10% (i.e., comparator; usual care), with a 5% margin for PE-FU (i.e., 15%). The routine follow-up takes place at 3, 12, and 24 months after surgery (i.e., 3 follow-up assessments with biplanar full spine radiographs = 6 radiographs). The incidence of adding-on per radiograph is 1.7% (i.e., 10%/6) for the control group/S-FU group. The risk of adding-on for the investigational group/PE-FU group will be 15% (prevalence of 10% with a 5% margin for PE-FU). The expected extra number of radiographs in the post-surgery group is 5% (expert opinion). Therefore, the incidence of adding on per radiograph is expected to be 14.3% (i.e., 15%/1.05). For the increase in incidence/radiograph from 1.7% to 14.3%, the calculated sample size is 69 patients per arm (given a 95% CI and 80% power). Considering a 10% dropout and/or loss to follow-up, the final sample size is 76 patients per treatment arm for the post-surgery group.

Based on the above (literature and expert opinion), for this study a total of 812 patients is required (alpha 0.05; power 0.80). This means 66 per arm for the RCT pre-treatment, 61 per arm for the RCT post-brace, and for the RCT post-surgery 76 per arm (subtotal of patients in the RCTs is 406). The preference cohorts consist of the same arms as the three RCTs. For each arm (preference cohort) a similar number of patients is required (subtotal of patients in the preference cohorts is 406 patients).

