### Randomization and blinding

After obtaining informed consent, patients will either be randomized or allocated to the protocol of their preference. Randomization is performed according to a minimization algorithm in a 1:1 ratio to either the standard follow-up protocol (S-FU) or the patient-empowered follow-up protocol (PE-FU). Randomization will be performed in CASTOR EDC (www.castoredc.com), an online secured study and data-management system with built-in randomization (random permuted block size 2:4). Considering the nature of this project, blinding to the follow-up allocation for patients and medical staff is not possible. The trial statistician will be blinded for the follow-up allocation.

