### Study interventions

#### Patient-empowered follow-up (PE-FU) protocol (Figure 2)

The PE-FU protocol consists of patient-reported outcome measures (PROMs), the Scolioscope and clinical assessment including physical examination by the physician. The Scolioscope is a self-assessment tool that measures the trunk rotation, similar to what is measured with the Bunnell scoliometer (Figure 3). At baseline and at last follow-up (24 months) biplanar radiographs are taken. Instead of routine radiographs, at all intervening follow-up visits radiographs will only be taken when curve progression or postoperative complications are suspected based on so-called “sense of alarm” criteria, which is a signal for the treating physician to consider whether a radiograph is appropriate.

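### The post-surgery sample size counts S-FU in single images and PE-FU in examinations; counted in examinations, 69 evaluable patients per arm give about 64% power on the plan's own method, not 80%.

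*Protocol article*

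**What the plan says.** The appendix sizes each of the three randomised trials separately, for superiority of PE-FU in the rate of events per radiograph. For the post-surgery trial it starts from per-patient risks:

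- S-FU: "The expert opinion for clinically relevant prevalence of adding-on is 10% (i.e., comparator; usual care".
- PE-FU: "The risk of adding-on for the investigational group/PE-FU group will be 15% (prevalence of 10% with a 5% margin for PE-FU".

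It then converts each risk to a rate per radiograph:

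- S-FU: "The incidence of adding-on per radiograph is 1.7% (i.e., 10%/6) for the control group/S-FU group". The six are follow-ups at 3, 12 and 24 months, each biplanar and counted as two.
- PE-FU: "the incidence of adding on per radiograph is expected to be 14.3% (i.e., 15%/1.05". The 0.05 is the 5% of extra radiographs expected by expert opinion. The appendix does not say what the 1 stands for.

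From these two rates, "the calculated sample size is 69 patients per arm (given a 95% CI and 80% power". With 10% added for dropout this becomes 76 per arm, which feeds the overall figure: "for this study a total of 812 patients is required (alpha 0.05; power 0.80".

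The PE-FU schedule is in the section on the patient-empowered protocol: "At baseline and at last follow-up (24 months) biplanar radiographs are taken". At the visits in between, radiographs are taken only on suspicion.

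**The concern.** A rate per radiograph can be compared between arms only if a radiograph means the same thing in both. Here a biplanar examination appears to count as two in the S-FU divisor and as one in the PE-FU divisor. That makes the S-FU rate look half as large, relative to PE-FU, as it would in a common unit. The error favours the trial: it enlarges the planned contrast and so shrinks the required number.

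The appendix relies on each randomised trial having its own 80% power. If the post-surgery trial falls short of that on the method used to size it, a null result there could be read as stronger evidence of no difference than it is.

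**Working it through.** **Inputs.** From the appendix: per-patient risks of 10% (S-FU) and 15% (PE-FU), divisors of 6 and 1.05, 80% power, alpha 0.05 (taken as two-sided from the reference to a 95% CI) and 69 per arm before dropout. Allocation is 1:1 (Randomization and blinding).

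**Formula.** Normal approximation for two proportions with unpooled variance:

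n per arm = (1.96 + 0.84)² × [p1(1 − p1) + p2(1 − p2)] / (p1 − p2)², where the squared term is 7.849 with unrounded quantiles.

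**Step 1: reproduce the plan.**

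- Post-surgery, 1.67% v 14.29%: 7.849 × (0.01639 + 0.12245) / 0.015924 = 68.4, so 69, as stated.
- Pre-treatment, 5.75% v 23.3%: 59.2, so 60, as stated.
- Post-brace, 5.75% v 24.3%: 54.1, so 55, as stated.

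All three match, so this is the plan's formula. It treats each patient as one observation.

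**Step 2: identify the units.**

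| | Follow-up examinations | Follow-up images | Divisor used |
|---|---|---|---|
| Post-surgery S-FU | 3 | 6 | 6 |
| Post-surgery PE-FU | 1 scheduled, plus 5% | 2 scheduled, plus 5% (2.10 if the extra films are biplanar) | 1.05 |
| Pre-treatment and post-brace S-FU | 4 | 5 (three uniplanar, one biplanar) | 4 |

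The divisor 1.05 matches examinations and not images. The other two trials also divide by assessments. Only the post-surgery S-FU divisor is in images.

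**Step 3: one unit in both arms, examinations.** S-FU 10%/3 = 3.33%; PE-FU 15%/1.05 = 14.29%.

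- Rate ratio: 14.29/3.33 = 4.3, against 14.29/1.67 = 8.6 as planned.
- Risk difference: 11.0 points, against 12.6 as planned, which is 13% smaller.
- Standard error at 69 per arm: √[(0.03222 + 0.12245)/69] = 0.0473. Then 0.1095/0.0473 = 2.31, and power = Φ(2.31 − 1.96) = 63.8%. Pooled variance gives 62.4%.
- With all 76 per arm analysed: 68.0%.
- Number for 80% power: 7.849 × 0.15467 / 0.011995 = 101.2, so 102 per arm before dropout.
- Effect detectable with 80% power at 69 per arm, against 3.33%: about 17.5%.

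**Step 4: secondary check in images.** S-FU 10%/6 = 1.67%; PE-FU 15%/2.10 = 7.14%, assuming that the extra films are biplanar. Power at 69 per arm is 35.3%, and 217 per arm would be needed for 80%. This spreads the risk over more images while still allowing one observation per patient, which lowers power mechanically, so it is not an equal alternative to Step 3.

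**The case against.** **The 1 in 1.05 is not defined.** This is correct; reading it as one examination is an inference, and the follow-up scheme in Figure 2 is not available in the text. The inference is strong, though. The only scheduled PE-FU follow-up imaging is biplanar, so in images the divisor could not be close to 1.

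**The 13% loss in risk difference is modest.** A reader might infer from the halved ratio that half of the planned effect is an artefact. The documents do not support that. Only the ratio halves, while the formula behind 69 works on the difference. The power still falls to 64%, because the difference is smaller and the S-FU variance term is larger (0.0322 against 0.0164).

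**The planned test does not use one observation per patient.** This is the strongest objection. The data analysis section divides radiographs with consequences by all radiographs and applies Pearson's chi-square test. With corrected units, 69 patients per arm supply about 69 × 3 = 207 and 69 × 1.05 = 72 examinations. Treated as independent, these give nominal power of about 72% (unpooled formula) or 85% (pooled). Both figures ignore clustering of examinations within patients, so they do not rescue the design. They do show that 64% belongs to the sample-size convention and is not the established power of the primary test.

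**The 35% figure might be read as the trial's real power.** The documents do not support that either, for the reason given in Step 4.

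**Conclusion.** The mismatch stands. The post-surgery calculation divides by images in one arm and, on the only reading that fits the PE-FU schedule, by examinations in the other. This also departs from the assessment count used for the other two trials. The stated 80% is therefore wrong on the plan's own method, and the figure to cite is about 64%.

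That figure rests on five things: the plan's risks of 10% and 15%, its 5% of extra radiographs, its unpooled two-sided formula, one observation per patient, and 69 evaluable patients per arm. It does not establish how much power the radiograph-level primary analysis will have; that would need an allowance for clustering. The pre-treatment and post-brace calculations do not have this S-FU image count, and their stated sizes reproduce.

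**What to change.** In the appendix, post-surgery group:

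1. Use the imaging examination as the unit in both arms: 10%/3 = 3.3% for S-FU and 15%/1.05 = 14.3% for PE-FU. State that the 1 in 1.05 is the 24-month examination, if that is what was meant.
2. Restate the power as about 64% at 69 evaluable patients per arm, or keep 69 and state the effect it can detect with 80% power, about 3.3% against 17.5%.
3. Add a sentence saying that this figure takes one observation per patient and does not describe the radiograph-level chi-square test.

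In the data analysis section, state that a biplanar examination counts once in the post-surgery primary outcome, so that the analysis uses the same unit as the sample size.

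The cost is new wording, one recalculated figure and a less favourable stated power. The correction itself needs no extra patients. Restoring 80% at the planned effect would be a separate decision, at 102 per arm before dropout.
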